##### Measures of Secondary Outcomes

*Overall Anxiety Severity and Impairment Scale [OASIS*
*(**36*, *37**)**]*. The OASIS is a five-item instrument that assesses the frequency and intensity of anxiety symptoms during the past week. In addition, it measures interference in work and academic, social, and daily life domains, as well as avoidance behaviors. The items are rated on a Likert-type scale (0–4). The psychometric properties are good in terms of internal consistency (α = 0.86), convergent and discriminant validity, and sensitivity to change (α = 0.86).

*Overall Depression Severity and Impairment Scale [ODSIS*
*(**38*, *39**)**]*. The ODSIS is a six-item questionnaire that assesses the frequency and intensity of depression symptoms during the past week. In addition, it measures interference in work and academic, social, and daily life domains, as well as avoidance behaviors. The items are rated on a Likert-type scale (0–4). The psychometric properties are good in terms of internal consistency (α = 0.93).

*Hopelessness Scale [HS*
*(**40**)**]*. It is a questionnaire that measures the level of hopelessness. It is made up of 20 items with dichotomous responses (True or False). It presents adequate internal consistency (α = 0.93) and has been validated in the Spanish population (41).

*The Positive and Negative Affect Schedule [PANAS*
*(**42*, *43**)**]*. The questionnaire includes 20 adjective items, 10 assessing positive affect (PANAS-P) and 10 assessing negative affect (PANAS-N). Respondents are asked to rate the extent to which they experienced each emotion within a specified time period, using a 5-point scale (1 = Very slightly or not at all; 5 = Very much). Both affect subscales showed adequate internal consistency: PANAS-P (α =0.89) and PANAS-N (α =0.91).

*Quality of Life Index-Spanish Version [QLI*
*(**44*, *45**)**]*. It is a 10-item index of perceived quality of life. It refers to physical and emotional wellbeing, functioning at work, personal relationships, self-independence, support in the community and from an emotional point of view, spiritual wellbeing, and overall perceived quality of life. The items are rated on a Likert scale (0–10) where higher scores indicate higher perceived quality of life. The psychometric properties are good for both internal consistency (α =0.89) and test-retest reliability (*r* = 0.87).

*Opinion and Expectations of Treatment Scale [OTSM*
*(**46**)**]*. This scale was designed and developed by members of the research team, based on an adaptation of another opinion and expectations questionnaire (46). The constructs this scale assesses are: opinion, acceptance and satisfaction with the skills training program, and changes in the participants after completing each module. The questions refer to the rationale for the intervention, recommendations for the program, satisfaction with the program, and usefulness and expectations of the skills training. The items are rated on a Likert-type scale ranging from 0 “Not at all” to 10 “Very much.”

*Mini-Mental Adjustment to Cancer Scale [MINI-MAC*
*(**47**)**]*. The MINI MAC evaluates the different ways of coping in cancer patients. It is a self-rating questionnaire made up of 29 items that measure five dimensions of coping: fighting spirit, helplessness-hopelessness, anxious preoccupation, fatalism, and cognitive avoidance. The items are rated on a Likert scale (1–4). The Spanish version of the MINIMAC (48) showed good psychometric properties for all the subscales (fighting spirit α =0.60, helplessness-hopelessness α =0.82, anxious preoccupation α =0.90, fatalism α =0.70, and cognitive avoidance α =0.80).

*The Posttraumatic Growth Inventory [PTGI*
*(**49*, *50**)**]*. The PTGI is a 21-item questionnaire that assesses the perception of personal benefits in survivors of a traumatic event. A Likert response format with six categories is used, with scores ranging from 0 (no change) to 5 (very high degree of change) in a positive sense; the higher the score, the greater the change perceived. The PTGI is composed of five dimensions: relating to others, new possibilities, personal strength, spiritual change and a better understanding of spiritual matters and stronger religious beliefs, and a new appreciation of life. The PTGI shows good internal consistency (α =0.80).

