As we can see in the aforementioned RCTs, MCP has been compared to waiting list, TAU with the general practitioner, and active treatments such as supportive therapy. To expand the data supporting the efficacy of MCP for cancer patients, it would be necessary to compare MCP to other active therapies such as CBT. According to the data, no previous studies have compared MCP to active treatments such as CBT for cancer patients, which is the general objective of this study.

The aims of the proposed study are: the first objective is to verify the efficacy of the MCP intervention for Spanish participants with cancer in an RCT comparing it to CBT. The second objective is to analyze the feasibility and acceptance of MCP in Spanish participants with cancer. The third objective is to analyze whether the changes produced in the MIL dimensions (presence, search, comprehension, purpose, and mattering) will predict changes in anxiety, depression, quality of life, etc.

We propose the following hypothesis: (a) After the intervention, all the participants in the two treatment conditions (MCP vs. CBT) will improve on MIL, anxiety, depression, and quality of life; however, the participants in the MCP condition will improve more than those in the CBT condition; (b) After the intervention, both interventions will have good acceptance by the participants, but the MCP condition will have greater acceptance than the CBT condition; (c) The changes produced in the MIL dimensions (presence, search, comprehension, purpose, and mattering) after the intervention will be related to changes in anxiety, depression, and quality of life.

In this article, we present the study protocol.

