Session 1: Concepts and Sources of Meaning.Introductions; review of concepts and sources of meaning; Meaningful Moments experiential exercise; homework is to read Man's Search for Meaning and reflect on the Session 2 experiential exercise.Session 2: Cancer and Meaning.Discussion of sense of identity before and after cancer diagnosis; Who am I? experiential exercise; homework is to reflect on the Session 3 experiential exercise.Session 3: Historical Sources of Meaning (Past Legacy).Discussion of life as a legacy that has been given (past); Historical Sources of Meaning-Past experiential exercise; homework is to reflect on the Session 4 experiential exercise.Session 4: Historical Sources of Meaning (present and future).Creation of lifeline. Own legacy development. Exercises: Reflection on the autobiography (in session and at home). Evaluate how situations are approached, objectives they had and that have been achieved. Explore a future legacy.Session 5: Attitudinal Sources of Meaning: Encountering Life's LimitationsDiscussion of confronting limitations imposed by cancer, prognosis, and death; Encountering Life's Limitations experiential exercise; introduction to Legacy Project; homework is to reflect on the Session 6 experiential exercise.Session 6: Creative Sources of Meaning: Engaging in Life Fully.Discussion of creativity, courage, and responsibility; Creative Sources of Meaning experiential exercise; homework is to reflect on the Session 7 experiential exercise.Session 7: Experiential Sources of Meaning: Connecting with LifeDiscussion of experiences as sources of meaning, such as love, nature, art, and humor; Love, Beauty, and Humor experiential exercise; homework is to complete the Legacy Project for presentation in Session 8.Session 8: Transitions: Reflections, and Hopes for the Future.Review of sources of meaning as resources, reflections on lessons learned; Hopes for the Future experiential exercise; goodbyes.

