#### Cognitive Behavioral Psychotherapy

The intervention lasts 2 months and includes 8 sessions that follow a 2-h group format on a weekly basis, with the following sessions (21):

Session 1: Presentation of psychotherapy, establishing the goals of psychotherapy. Presentation of the participants. Updated information about psychological consequences of cancer.Session 2: Increase in enjoyable activities. Behavioral activation. Progressive muscle relaxation training. Slow breathing training.Session 3: Cognitive model of coping with cancer. ABC model. Psychoeducation on negative thoughts. Training in detecting negative thoughts. Presentation of cognitive distortions.Session 4: Training in cognitive restructuring techniques.Session 5: Training in problem-solving skills.Session 6: Being aware of our own needs. Self-care. Assertiveness skills training.Session 7: Setting goals for the future.Session 8: Summary, relapse prevention, and end of psychotherapy.

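### The acceptance scale (OTSM) is described as rating a skills training programme, which fits CBT but not MCP, so the between-arm acceptance comparison in hypothesis (b) is open to item-content bias

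*Protocol article*

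**What the plan says.** In the protocol article, the Introduction sets out hypothesis (b): both treatments will be well accepted, but "the MCP condition will have greater acceptance than the CBT condition". This is a comparison between arms.

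The OTSM appears under Measures of Secondary Outcomes. Its constructs are given as "opinion, acceptance and satisfaction with the skills training program, and changes in the participants after completing each module". The question content follows in two parts. The first is general: "The questions refer to the rationale for the intervention, recommendations for the program, satisfaction with the program". The second is tied to a particular kind of treatment: "usefulness and expectations of the skills training". Items are rated from 0 to 10. The research team made the scale itself by adapting an existing questionnaire. The opening of the Measures section says that both arms complete every primary and secondary measure.

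The Interventions section describes the two programmes. MCP begins with "review of concepts and sources of meaning; Meaningful Moments experiential exercise" and continues in that style. CBT includes "Training in problem-solving skills" and "Assertiveness skills training".

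**The concern.** A comparison of two arms on a rating scale presumes that the questions refer to the same thing in both. Here the scale is described in the vocabulary of one kind of treatment. A CBT participant asked how useful the skills training was can answer literally. An MCP participant asked the same question has no obvious referent and may rate it low, leave it blank, or read it as meaning the group programme in general. An arm difference on those questions would then mix acceptance with whether the question applies. If MCP participants skip them, any summary score would rest on different items in the two arms.

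What is at stake is the comparative half of hypothesis (b). No other scored acceptance measure is listed to check the OTSM against. The interviews in the qualitative part of Data Analyses have no stated topic, and the article describes no score from them.

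**Working it through.** No arithmetic applies. The check sets the description of the scale beside the description of each arm.

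**Step 1: skills training against CBT.** In the Cognitive Behavioral Psychotherapy section, training is named in session 2 (muscle relaxation, slow breathing), session 3 (detecting negative thoughts), session 4 (cognitive restructuring), session 5 (problem-solving) and session 6 (assertiveness). That is 5 of 8 sessions. The article does not call CBT as a whole a skills training programme, but a question about skills training has a clear object there.

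**Step 2: skills training against MCP.** The eight sessions in the Meaning-Centered Group Psychotherapy section comprise discussion, experiential exercises, reflection at home, a lifeline and autobiography exercise, and a legacy project. Training in a skill is named in 0 of 8 sessions. A question about skills training has no stated object in this arm.

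**Step 3: module against both arms.** Both programmes are described as eight weekly sessions, and neither is divided into modules. This term misfits both arms equally, so it does not favour either. It does suggest that the description was not fitted to this trial.

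**Step 4: which questions are affected.**

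| OTSM question content | Object named | CBT | MCP |
|---|---|---|---|
| Rationale | the intervention | applies | applies |
| Recommendation | the programme | applies | applies |
| Satisfaction | the programme | applies | applies |
| Usefulness | the skills training | applies | no stated object |
| Expectations | the skills training | applies | no stated object |

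The construct sentence attaches satisfaction to the skills training programme, but the sentence on question content attaches it to the programme. The table follows the latter because it is closer to what participants are asked.

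**Step 5: link to the hypothesis.** Both arms complete the scale, hypothesis (b) compares the arms on acceptance, and no other quantitative acceptance measure is listed. Nothing elsewhere in the article corrects or qualifies the OTSM description.

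**Step 6: size.** Sizing a bias would need the number of affected items, how much their misfit shifts an MCP participant's rating, how the items are combined, and the score's standard deviation. The article gives none of these.

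**The case against.** The strongest reply is that the article summarises the scale and reproduces no item. A condensed article may leave questionnaire wording to the full protocol. The team adapted the instrument itself, its name refers to treatment in general, and the form participants see may already be neutral. The use of module, which fits neither arm, suggests loose phrasing as much as a scale written for CBT. Much of the listed content is general in any case.

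Most of this stands, and it limits the point. It rules out saying that MCP participants will be asked about something they did not receive, because the items are not shown. It also confines the concern to usefulness and expectations. It does not remove the mismatch. The skills-training wording occurs in the sentence describing the questions as well as in the list of constructs, and it conflicts with the article's own account of MCP. That is a statement that does not fit, which differs from a detail left to a fuller document.

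A reader might go further and infer that the comparison is biased, probably against MCP. The document does not support this. MCP participants could rate the questions low, skip them, or reinterpret them, and these responses need not push the result the same way. A reader might also infer that the trial cannot meet its acceptance objective. That is too strong as well: the second objective concerns the feasibility and acceptance of MCP among Spanish participants and is not comparative, the general questions remain usable, and interviews are planned.

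**Conclusion.** The point holds in a limited form. As described, the OTSM's usefulness and expectation questions do not have the same meaning in the two arms, so the acceptance comparison in hypothesis (b) is open to item-content bias of unknown direction and size. The rationale, recommendation and satisfaction questions are not affected.

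This rests on two assumptions: that the article's description reflects the items participants see, and that the listed sessions fairly represent each programme's content. If the actual items are already neutral, only the description is wrong.

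The matter touches one secondary measure and leaves the meaning-in-life outcomes, the sample size and the efficacy analysis alone. It is still worth acting on, because a stated hypothesis depends on this one scale and the remedy costs almost nothing.

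**What to change.** Word every OTSM item neutrally and identically in both arms, with *the group programme* in place of the skills training terms and *session* in place of module. Correct the OTSM description under Measures of Secondary Outcomes to match. If the items in use are already neutral, correcting the description is enough.

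The Participants section calls the study ongoing, so some forms may already be complete. If those carried skills-training wording, base the hypothesis (b) comparison on the items that apply to both programmes (rationale, recommendation, satisfaction) and report the remaining items descriptively. Fix that item list before anyone looks at OTSM results by arm.

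The cost is rewording a few items in a scale the team adapted itself, or a restricted scoring key. The small downside is less direct comparability with earlier use of the scale and, under the restricted key, a narrower acceptance score.

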### Data Analyses

For data analysis, the Consort guidelines will be followed. Prior to analyzing whether MCP was more effective than CBT, we will verify that the two experimental conditions are similar in all the sociodemographic variables, such as age, sex, marital status, and education. In addition, we will verify that the two conditions are similar in terms of the percentage of participants who have received chemotherapy, radiotherapy, and surgery. To do so, we will use comparison of means (Student's t) for the continuous variables and chi square for the categorical variables. Moreover, the intention-to-treat principle will be used when analyzing pre- and post-treatment data and at the 6-month follow-up, using mixed-effects models with full information and maximum likelihood estimation. This method has been recommended due to its flexibility in handling missing data (51). To complement the MANOVA results and *post hoc* comparisons, effect sizes will be calculated using the standardized mean difference proposed by Cohen (52). These effect sizes will be calculated to assess changes within and between groups, all based on a pooled standard deviation. MANCOVAS will be carried out to find out if there are differences in the participants' response to the two experimental conditions depending on the type of medical treatment administered (surgery, chemotherapy, or radiotherapy), the stage of the cancer before the start of medical treatment, and whether the patient has a relapse during the psychological treatment. Moderation and mediation analyses will be performed to investigate possible mediators of change during treatment, such as meaning in life or coping style. Although per-protocol analyses (only analyses of data from participants who complete the treatment) suffer from selection bias, they will also be conducted because they allow conclusions to be drawn about the maximum efficacy of the intervention in participants who are fully compliant with treatment. However, when the trial is completed, the analytical methodology for controlled clinical trials will be reviewed before analyzing the data to select the most appropriate analytical procedures.

For the qualitative study, semi-structured in-depth interviews will be used. The research design will be carried out following the criteria established by Cooke, Smith, and Booth (53). Data will be analyzed using the consensual qualitative research method. Data reporting will be carried out following the COREQ guidelines (54).

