**Methods:**

The aims of the proposed study are: the first objective is to verify the efficacy of the MCP intervention for Spanish participants with cancer in a randomized control trial (RCT) comparing it to CBT. The second objective is to analyze the feasibility and acceptance of MCP in Spanish participants with cancer. The third objective is to analyze whether the changes produced in the meaning in life dimensions (presence, search, comprehension, purpose, and mattering) will predict changes in anxiety, depression, quality of life, etc. Our research team adapted MCP for Spanish participants with cancer. This paper presents the study protocol. The study design consists of a two-arm RCT with two conditions: MCP and CBT, where participants will be randomized to one of the two groups. Eligible participants will be adults with stage I, II, and III cancer who were treated with curative intent and had completed their main medical treatment (surgery, radiotherapy, or chemotherapy). Participants will be assessed at pretreatment, post-treatment, and 6-month follow-up. The intention-to-treat principle will be used when analyzing data, using mixed-effects models with full information and maximum likelihood estimation.

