### Procedure

Cancer survivors who have been treated at the Valencian Institute of Oncology will be offered the opportunity to participate in the study. Once they have signed the informed consent, a clinical psychologist who is an expert in cancer will carry out two evaluation sessions to verify that they meet all the inclusion criteria. Once evaluated, randomization will be carried out by an independent researcher who is blind to the evaluation of the participants. At all times, the randomization sequence will be concealed from the clinicians participating in the study. The evaluation will be carried out by independent evaluators who are blind to the experimental conditions. Subsequently, each participant will begin their group intervention in the condition to which they have been assigned. Participants will not receive any other psychological or psychiatric treatment during this study. When the psychotherapy is over (MCP or CBT), the evaluation will be carried out again. A follow-up will be carried out at 1 month, at 3 months, and at 6 months. The evaluation will be carried out online before and after finishing the treatment and in the follow-ups. All the interventions will be performed by clinical psychologists or general health psychologists with a Master's degree and previous training in the application of the programs. All the interventions will be carried out through online video conferences in both treatment conditions.

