### Measures

After reviewing the literature, an evaluation protocol was designed that includes the main instruments that have been commonly used by authors working in this field (29), as well as some additional instruments that we consider relevant to the hypotheses proposed. In all cases, the Spanish validations of the assessment instruments will be used; if they do not exist, the validations will be carried out by the researchers of this study. Participants in both treatment conditions will complete all primary and secondary outcome measures at five time points: before and after treatment and at 1-month, 3-month and 6-month follow-ups.

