## Discussion

The first objective of this proposed study will be to analyze the efficacy of the Spanish adaptation of MCP for cancer survivors. For this aim, we have designed an RCT in which we will compare MCP to CBT in people with cancer, with three assessment times: pre-treatment, post-treatment, and 6-month follow-up. In previous studies on the efficacy of MCP, it has been compared to waitlist, TAU, therapeutic massage, and supportive social therapy (8, 9, 12, 13). In order to broaden the knowledge about the efficacy of MCP, in this study we compare it to CBT. In previous studies, CBT has shown its effectiveness in reducing anxiety and depression, facilitating cancer adjustment, and improving quality of life (21, 22). Therefore, if MCP is equally effective or more effective in reducing anxiety and depression and improving quality of life, hopelessness, and meaning in life, this result would suggest that MCP could be a treatment of choice for people with cancer.

The second objective of this proposed study will be to analyze the feasibility and acceptance of MCP in Spanish participants with cancer. The concepts and premises of logotherapy, such as meaning-making, vital goals, the concepts of responsibility, freedom, courage, legacy, and will to meaning, or meaning in life, are subject to cultural, religious, and social factors specific to each culture (19). Given that all the RCTs on the efficacy of MCP have been carried out in an English-speaking population, it is necessary to analyze the extent to which the Spanish participants accept the program and are comfortable with it, as well as their opinions and expectations about it, in order to improve adherence and future implementation.

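### Outcomes are collected at five time points but the mixed model names only three, which leaves the 1- and 3-month data unused and can weaken the 6-month comparison

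*Protocol article*

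**What the plan says.** The protocol article gives two schedules.

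- **Five assessments.** Measures says that both arms complete all primary and secondary outcomes "at five time points: before and after treatment and at 1-month, 3-month and 6-month follow-ups". Procedure agrees: "A follow-up will be carried out at 1 month, at 3 months, and at 6 months".
- **Three assessments.** The Methods part of the Abstract says "Participants will be assessed at pretreatment, post-treatment, and 6-month follow-up". The Discussion describes the trial as one "with three assessment times: pre-treatment, post-treatment, and 6-month follow-up".

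Data Analyses follows the shorter list. It says that "the intention-to-treat principle will be used when analyzing pre- and post-treatment data and at the 6-month follow-up". The stated tool is a likelihood-based mixed model, which the section justifies by its flexibility with missing data. The 1- and 3-month assessments appear in no analysis. The section closes by saying that the analytical methods will be reviewed once the trial is completed, before the data are analysed.

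**The concern.** A likelihood-based mixed model protects against dropout only if, given the data in the model, the chance of being lost does not depend on the unseen values. A participant lost between post-treatment and 6 months may have given scores at 1 and 3 months. If those scores drive the loss and are left out, the condition that the plan relies on can fail although the data that would satisfy it are in hand.

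This matters because the trial expects 30% dropout, the Discussion lists dropout as its first limitation, and the 6-month visit is meant to show whether results last. The two schedules also leave the reader unsure how many assessments the trial has.

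**Working it through.** **1. The schedules side by side**

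| Section | Pre | Post | 1 m | 3 m | 6 m |
|---|---|---|---|---|---|
| Procedure | yes | yes | yes | yes | yes |
| Measures | yes | yes | yes | yes | yes |
| Abstract | yes | yes | – | – | yes |
| Data Analyses (mixed model) | yes | yes | – | – | yes |
| Discussion | yes | yes | – | – | yes |

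Five waves are collected and three are named for analysis, so 5 − 3 = 2 have no stated use.

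**2. Inputs**

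- From Sample Size: 59 per arm, 30% dropout, planned effect 0.60 SD. The 45 per arm before dropout reproduces: an exact two-sided t-test at alpha 0.05 and power 0.80 needs 44.6 per arm. The 59 per arm is 45 × 1.3 = 58.5, rounded up. It is used here only as the stated size.
- Assumed, because the protocol gives none: the correlations between waves, and when and why participants are lost.

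**3. Why the omitted waves can matter**

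With three waves, the model fills in a lost 6-month score from the pre- and post-treatment scores. Suppose loss depends on the 3-month score. Then, roughly, the bias in one arm is β × δ. Here β is the slope of the 6-month score on the 3-month score, given pre and post. δ is how far the retained participants' 3-month scores sit from what their pre and post scores predict. The bias in the arm difference is β × (δ in MCP − δ in CBT). Three things follow:

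- If all loss precedes post-treatment, the lost participants have only a baseline score under either model, so the two analyses agree.
- If the mechanism is the same in both arms and there is no true difference, the two δ terms cancel.
- If only one arm loses participants in this way, nothing cancels.

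**4. Size of the bias**

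Simulated trials of 59 per arm, about 30% lost, adjacent-wave correlation about 0.8, no true difference. Loss depends on the last score with a log-odds slope of 1.2 to 2.0 per SD. Bias is at 6 months, in SD units:

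| Pattern of loss | Three waves | Five waves |
|---|---|---|
| All before post-treatment, score-driven in one arm | −0.002 to −0.011 | identical |
| After post-treatment, same slope (1.2) in both arms | 0.007 | 0.006 |
| 20% before post-treatment, the rest after; slope 1.2 in one arm | about 0.04 | about 0.01 |
| After post-treatment, one arm only, slope 1.2 to 2.0 | 0.05 to 0.11 across separate runs | 0.02 or less |

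The SD of the estimate was 0.21 to 0.22 with either model in the one-arm case. Against the planned effect, 0.1 / 0.60 is about 17%. Against the sampling SD, 0.1 / 0.21 is about one half.

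A deliberately harsher case was also run with very large samples: a true difference of 0.60, and 30% lost after month 3 in opposite directions in the two arms. Three waves estimated 0.67 to 0.79 and five waves 0.59 to 0.61. This marks an extreme, not an expectation.

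**5. Precision**

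The variance of the 6-month difference was computed from the information matrix, with correlations of 0.5 to 0.85, either constant or decaying with time. Ratio of three-wave to five-wave variance:

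- all loss before post-treatment: 1.00
- loss spread evenly over the four intervals: 1.01 to 1.04
- all loss between 3 and 6 months: 1.03 to 1.11

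The largest ratio, 1.11, is a standard-error ratio of √1.11 ≈ 1.05. Any gain therefore lies mainly in bias, not precision.

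**The case against.** The strongest reply is that the harm may be nil. Sample Size ties the 30% to loss during the treatment programme. If all of it occurs there, the 1- and 3-month scores change nothing, as the first row of the bias table shows. The larger figures need loss that comes late, follows the scores and differs between arms, and the documents do not say that it will. This stands, and it is why the size is given as a range from zero. It does not remove the point, because assessments continue for six months after treatment and nothing says that loss stops at post-treatment.

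A second reply is that Data Analyses does not say that only these time points will be used, and that its closing sentence leaves the methods open to review. That also stands in part: the omission is not final. But the sentence commits to no use of the two waves, and choosing the waves once the trial is completed is an avoidable freedom. Nor can condensation in a journal article explain the conflict, since the article itself states both schedules.

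A reader might also infer that the third objective, whether changes in meaning predict changes in symptoms, cannot be answered with three waves. The documents do not support this. Pre-to-post change in meaning followed by post-to-6-month change in symptoms is time-ordered and needs only three. Data Analyses says that "Moderation and mediation analyses will be performed to investigate possible mediators of change during treatment" but fixes no time points for mediator or outcome, so it does not prescribe a same-interval correlation. The 1- and 3-month visits would add later outcome points to such an analysis. They come after treatment and cannot supply a mid-treatment measure.

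**Conclusion.** The point holds as a contradiction about the schedule combined with an analysis that names fewer waves than are collected. The contradiction is plain from the text and rests on no assumption.

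The statistical consequence is conditional. The three-wave bias at 6 months runs from 0 to about 0.1 SD, depending on when loss occurs and whether it follows the scores differently in the two arms. With five waves it is about 0.02 SD or less, and the standard error is practically unchanged. These figures rest on assumed correlations and dropout patterns and on about 30% loss. They show what could happen and do not predict what will. It would go too far to say that the 6-month result is biased, or that the third objective is out of reach. A change is still worth making, because five waves did no worse in any pattern examined and the data are already scheduled.

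**What to change.** 1. Fit the mixed model to all five waves, with time as a categorical factor crossed with arm and an unstructured covariance. Estimate the post-treatment and 6-month arm contrasts from that one model. The protocol names no primary time point, so the text should state both contrasts explicitly.
2. Reconcile the Abstract, Data Analyses and Discussion with Procedure and Measures, so that one schedule appears throughout.
3. If the 1- and 3-month scores are also used for the third objective, say so as an addition: pre-to-post change in meaning, then later change in symptoms.

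The cost is a few sentences of wording and a somewhat larger covariance matrix to estimate. No visit or questionnaire is added.
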